## Discussion

### Strengths and challenges

Systematic reviews assessing previous studies on TRE show positive effects on weight loss but there is limited knowledge about the effects on metabolic outcomes and PROMs as the latter are scarcely addressed [10, 11, 33, 35]. Furthermore, evidence from the primary care sector is lacking, and most studies have a duration of 8 to 12 weeks only, while the evaluation of adherence in weight loss approaches is crucial. Therefore, studies on the long-term effects of TRE are needed [10]. Patient populations in the primary care sector represent an unselected patient population as well as a broad spectrum of patients. Recruitment in primary care is advantageous, as this sector is highly relevant in terms of disease burden and social relevance in obesity. The INDUCT study addresses these research gaps by including PROMs such as sleep quality, feeling of hunger and quality of life. Also, the duration of the intervention in the INDUCT study is six months, with a 6-month follow-up giving the possibility to derive long term-effects of TRE.

Challenges in this study arose from the heterogeneity of the participating research practices and in consequence of the research tandem. INDUCT is the first study and first randomized controlled trial within the newly established research infrastructure FoPraNet-BW. While all participating practice teams have undergone a training on research in their practice, there is none to little experience in conducting a study in their own practice. Also, previous experiences with TRE differ a lot among participating practice teams. We propose that there is a learning curve within the research tandem regarding e.g. support and monitoring of study participants as well as data collection and management. All the named aspects could influence data quality. As every participating practice represents one study center within INDUCT, monitoring of the study prerequisites other approaches than monitoring a RCT with one study center only. Study nurses at the four participating departments of general practice therefore established new processes and made use of the digital research infrastructure.

Furthermore, we hypothesize that the handling of the newly developed software could differ between practices with effects on data quality and recruitment of patients for the study. The development of the digital research infrastructure is considered a constant process as software development continues during the entire duration of FoPraNet-BW based on feedback from all user groups.

As there is no structured treatment approach for obesity in GP in Germany, treatment as usual is difficult to define and to standardize. Therefore, treatment in the CG is expected to show a high variation, which will have an influence on the study results. In knowledge of this, we aimed to address aspects of care in the CG through the study diaries. Another major challenge is to retain participants assigned to the CG. We hypothesize that motivation to start the study is also a motivation for weight reduction, so there is a potential risk that participants from the CG try other weight management approaches. CG participants will all be offered to try TRE after the intervention phase of the INDUCT study and will have the opportunity to be supported by their GP practice. Loss to follow-up is expected in both groups. This loss of study participants is addressed by adding a 20% dropout-ratio into the sample size calculation.

### Patient and public involvement

The study diaries and questionnaires for participants and research practices were developed and piloted in a participatory process with the target groups. Information about the INDUCT study was provided to the research practices and the study participants in FoPraNet-BW via the project website [36], newsletters and the websites of the participating university institutions of general practice. Further information was provided to GP practice teams at CME-events such as the “Day of General Practice”.

The results of the INDUCT study will be presented and discussed with the participating practice teams and the expert advisory board, consisting of representatives from the healthcare sector and patient organizations. Furthermore, the results will be presented and discussed with the Citizens' Advisory Council as well as patient representatives. The Citizens’ Advisory Council was established in 2023 at the Institute of general practice at Freiburg university aiming to integrate the perspectives and needs of citizens concerning research in GP. Results from these discussions will be included in the dissemination of the study results. In order to inform both the general public and the medical community about the results of the INDUCT study, publications are planned via open access publications, the FoPraNet-BW project website and the website of the Initiative of German GPBRNs DESAM ForNet [36, 37]. Publications in simple lay language are also planned in collaboration with the Citizens' Advisory Board and patient representatives.

### Ethical considerations and data protection aspects

The INDUCT study was approved on 01.03.2023 by the Ethics Committee of the Medical Faculty of Tuebingen (097/2023BO2). The digital research infrastructure as part of the PBRN FoPraNet-BW was approved prior to the start of INDUCT in a consensual process among all ethics committees of the participating medical faculties at the participating universities under the leadership of the Baden-Wuerttemberg Medical Association (F-2022–059/ coord. B).

A comprehensive data protection concept for FoPraNet-BW was developed together with and approved by the data protection officers of the participating university hospitals (Tuebingen, Freiburg, Heidelberg, Ulm) and the University of Reutlingen. Part of the federated data infrastructure is that study teams at the university departments have access to pseudonymized data only, all personal data remains within the participating practices. In order to be able to collect data as part of the study, the study participants had to give their informed consent in their GP practice to participate.

### Trial status

At the beginning of the INDUCT study 41 research practices were part of the FoPraNet-BW. The recruitment process of the participants in these research practices was started in August 2023 and completed in December 2023. 149 eligible participants have been recruited in those 41 research practices. 12 months after the study inclusion a follow-up is planned. The last patient-out therefore is expected in December 2024.

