**Methods:**

INDUCT is a type hybrid I, randomized-controlled study conducted in 41 practices within the newly established general practice-based research network (GPBRN) in Baden-Wuerttemberg (FoPraNet-BW). The study population consists of patients with a Body Mass Index between 30–45 kg (kg)/m^2^. The intervention group receives TRE at the scheme 16:8 (16 h fasting; 8 h energy intake) while the control group receives care as usual. The primary outcome is change in body weight under a 6-month period of TRE. Secondary outcomes are related to the patient (e.g. quality of life) and the practice (e.g. knowledge about research in own practice). As the INDUCT study represents one of the first four use-cases within the Research Network Baden-Wuerttemberg (FoPraNet-BW), feasibility is a further secondary outcome. The target sample size is 208 patients with a 1:1 randomization. An intention-to-treat approach is used for data analysis.

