### Sample size

The target sample size for the INDUCT study is 208 patients with obesity based on previous studies, which stated that the clinically significant difference in body weight loss up to 24 weeks is 2.5%. The change in body weight of 2.5% corresponds approximately to ~ 2.2 kg for INDUCT participants (BMI ≥ 30 kg/m^2^) with an estimated average height of 172 cm [29]. Based on two studies, a standard deviation of 5 kg is assumed for within-group changes [8, 30]. A two-tailed independent t-test (alpha = 0.05; effect size d = 0.44) with statistical power of 0.8 was used to calculate the sample size of n = 83 per group (n = 166 total) to detect a difference in weight change of 2.2 kg (standard deviation: 5 kg) between the two groups. With a 20% dropout-rate, a total of n = 208 participants need to be recruited. Therefore, the aim was to recruit 4 to 5 participants from each participating research practice for the INDUCT study.

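### Recruitment closed at 149 against a target of 208, so the planned 80% power is not reached under any dropout rate, and the article does not say so

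*Protocol article*

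**What the plan says.** The Sample size section gives the test and effect size as "A two-tailed independent t-test (alpha = 0.05; effect size d = 0.44", and the target as "to detect a difference in weight change of 2.2 kg (standard deviation: 5 kg) between the two groups". The result is 83 per group: "with statistical power of 0.8 was used to calculate the sample size of n = 83 per group (n = 166 total". The allowance for loss follows: "With a 20% dropout-rate, a total of n = 208 participants need to be recruited". The abstract repeats the target: "The target sample size is 208 patients with a 1:1 randomization".

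The Trial status section reports that recruitment ran from August to December 2023, is complete, and that "149 eligible participants have been recruited in those 41 research practices".

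In the Discussion, under Strengths and challenges, the article expects loss to follow-up in both groups and says that the 20% built into the sample size calculation addresses it. It also calls retention of control participants a major challenge. The Study design and setting section describes the test of the clinical effect as confirmatory.

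No section compares 149 with 208, restates the power, or gives the difference that the achieved size can detect. The Outlook names strategies for better recruitment as a topic of the evaluation, but does not link this to the primary analysis.

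**The concern.** The article gives a design power, the size needed to reach it, and a final enrolment well short of that size, and leaves the three unreconciled. Recruitment had closed by the time of writing, so the final number was known.

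The interpretation of the primary result is at stake. A reader who takes 80% power from the Sample size section would put the chance of missing a true 2.2 kg difference at about 20%. With 149 recruited and the planned dropout, it is about 34%. A non-significant result would therefore say less against time-restricted eating in general practice than the stated design suggests. The dropout statement adds to the problem, because it tells the reader that attrition is covered when no reserve is left.

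**Working it through.** **Inputs.** From Sample size: two-sided independent t-test, alpha 0.05, power 0.80, difference 2.2 kg, standard deviation 5 kg, dropout 20%. From Randomization: 1:1 at patient level. From Trial status: 149 recruited, recruitment complete.

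**Step 1: reproduce the plan's figure.**
- Effect size: d = 2.2 / 5 = 0.44.
- Exact (noncentral t) sample size: 82.05 per group, rounded up to 83, so 166 in total. Power at 83 per group is 80.5%.
- Dropout: 166 / (1 − 0.20) = 207.5, rounded up to 208.

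The plan's 83, 166 and 208 all reproduce.

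**Step 2: compare with enrolment.**
- 149 / 208 = 0.716, or 72% of target.
- 166 − 149 = 17. Enrolment is 17 below the evaluable number before any loss.

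**Step 3: power at the achieved size.** Evaluable N = 149 × (1 − dropout), split about 1:1. The noncentrality parameter is 2.2 / SE, with SE = 5 × √(1/n₁ + 1/n₂). Power comes from the noncentral t distribution with n₁ + n₂ − 2 degrees of freedom. The last column is the difference detectable with 80% power.

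| Dropout | Evaluable (per group) | SE, kg | Power for 2.2 kg | Detectable, kg |
|---|---|---|---|---|
| 0% | 149 (75/74) | 0.82 | 76% | 2.31 |
| 20% | 149 × 0.8 ≈ 119 (60/59) | 0.92 | 66% | 2.59 |
| 30% | 149 × 0.7 ≈ 104 (52/52) | 0.98 | 60% | 2.77 |

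The normal approximation agrees closely: 76.6% with no dropout and 67.1% at 20%.

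**Step 4: expected precision at 20% dropout.** The 95% confidence interval half-width is t × SE = 1.98 × 5 × √(1/60 + 1/59) = 1.98 × 0.917 = 1.82 kg. At the planned 83 per group it would be about 1.97 × 5 × √(2/83) = 1.53 kg.

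**The case against.** The strongest reply is that nothing in the article is miscalculated. The sample size arithmetic is right. The sentence "with statistical power of 0.8 was used to calculate the sample size" describes a design input and does not claim that the trial as enrolled has that power. The figure of 149 is openly given, and any reader can set it against 208. All of this stands, so the a priori calculation should not be rewritten. It does not answer the point, however. Giving 149 in one section does not reconcile it with a target, a power and a dropout statement elsewhere that the enrolment overtakes.

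A second reply is that 66% is conditional, and this is also right. It assumes that the planned 20% is lost and that an unadjusted t-test is run on those who remain. The article announces an intention-to-treat approach but does not give the primary model or the handling of missing data, and a separate analysis plan may do so. With weight available for all 149, power is 76%. Covariates explaining about 9% of the variance would then restore 80%: 1 − (2.2/2.31)² ≈ 0.09. With 119 evaluable, about 28% would be needed: 1 − (2.2/2.59)² ≈ 0.28. The fair statement is therefore a range with its assumptions. Adjustment could recover some power, but the article does not state any.

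Two stronger readings are tempting and are not supported. A reader might infer that the sample size calculation itself is in error; it reproduces exactly. A reader might also compare the per-practice aim ("Therefore, the aim was to recruit 4 to 5 participants from each participating research practice") with the 41 practices and find that 41 × 4 to 41 × 5 gives 164 to 205, never 208. That is an approximate aim for a recruitment phase now over, its upper end is 3 short of the target, and the section does not tie it to a number of practices. It needs no correction.

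Finally, no passage says that a non-significant result would be read as absence of effect. That misreading is a risk left open by the article's silence, and the article does not itself make it.

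**Conclusion.** The point holds as an unaddressed shortfall. Under the plan's inputs the intended 80% power is not reached at any dropout rate: the ceiling is about 76%, the figure at the planned 20% dropout is about 66%, and at 30% it is about 60%. The detectable difference rises from the planned 2.2 kg to about 2.3, 2.6 and 2.8 kg respectively. The Discussion's statement that the 20% allowance addresses loss to follow-up is no longer true.

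These figures assume a standard deviation of 5 kg, an unadjusted two-sided t-test at 0.05, and that all 149 were randomised about 1:1. The article says recruited, not randomised. If fewer were randomised, power is lower. A smaller standard deviation or a baseline-adjusted analysis would raise it.

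**What to change.** Keep the Sample size calculation unchanged and identify it as the a priori plan. Add a short statement to Trial status, with cross-references from Sample size and from the dropout sentence in Strengths and challenges, along these lines:

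> Recruitment closed with 149 of the planned 208 participants (72%), fewer than the 166 evaluable participants required. Under the design assumptions, power to detect 2.2 kg is about 60–76% for dropout between 30% and 0% (66% at the planned 20%). At 20% dropout, the difference detectable with 80% power is about 2.6 kg and the expected 95% confidence interval half-width is about 1.8 kg. A non-significant result will be interpreted through its confidence interval in relation to 2.2 kg.

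The dropout sentence should say that the 20% allowance belonged to the planned size and was not achieved. If the primary model adjusts for covariates, the power under that model can be given alongside, with its assumption stated.

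The cost is a few sentences and a less favourable power figure. No participants, visits or trial procedures change.

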### Outlook

If TRE with the 16:8 scheme proved to be successful in regard to weight loss, metabolic aspects and further PROMs, while being safe, it can represent a concept that could be transferred to care in GP in Germany. Furthermore, the accompanying process evaluation is expected to identify facilitating factors and barriers that may be crucial for further implementation of TRE. In addition, valuable insights from conducting research within a GPBRN in Germany can be derived. One focus of the evaluation is also the development of strategies to improve recruitment of patients in their practices. Lessons learned from INDUCT can be used to plan further intervention studies with the research practices of the FoPraNet-BW and intervention studies in other GPBRN in general. Also, further intervention studies on weight management in GP practices could be planed based on the results of this study.

## Data Availability

No datasets were generated or analysed during the current study.

## Abbreviations

BMBF: Federal Ministry of Education and Research (Germany)
BMI: Body-Mass-Index
CFIR: Consolidated Framework for Implementation Research
CG: Control Group
CME: Continuing Medical Education
DESAM ForNet: Initiative of German Practice-Based Research Networks
DRKS: German Clinical Trials Register
FoPraNet-BW: Research Network Baden-Wuerttemberg/ Forschungspraxennetz Baden-Württemberg
GFR: Glomerular filtration rate
GP: General practice
GPBRN: General practice-based research network
HbA1c: Glycated hemoglobin
IF: Intermittent Fasting
IG: Intervention Group
INDUCT: Intermittent Fasting with obesity in general practice
kg: Kilogram
m^2^: Square meters
meDIC: Medical Data Integration Center
PROMs: Patient Reported Outcome Measures
REDCap: Research Electronic Data Capture
SPIRIT: Standard Protocol Items: Recommendations for Interventional Trials
TRE: Time-restricted eating
WHO: World Health Organization
